## Abstract

**Background:**

Although childhood sexual and/or physical abuse (CSA/CPA) is known to have severe psychopathological consequences, there is little evidence on psychotherapeutic interventions for adolescents and young adults suffering from post-traumatic stress disorder (PTSD). Equally sparse are data on moderators of treatment response on PTSD-related epigenetic changes, health care costs and loss of productivity, alterations in cognitive processing, and on how successful interventions affect all of these factors. Early treatment may prevent later (co)morbidity. In this paper, we present a study protocol for the evaluation of a newly developed psychotherapeutic manual for PTSD after CSA/CPA in adolescents and young adults – the Developmentally Adapted Cognitive Processing Therapy (D-CPT).

**Methods/design:**

In a multicenter randomized controlled trial (RCT) D-CPT is compared to treatment as usual (TAU). A sample of 90 adolescent outpatients aged 14 to 21 years will be randomized to one of these conditions. Four assessments will be carried out at baseline, at end of treatment, and 3 and 6 months after end of therapy. Each time, patients will be assessed via clinical interviews and a wide range of questionnaires. In addition to PTSD symptoms and comorbidities, we will evaluate moderators of treatment response, epigenetic profiles, direct and indirect costs of this disorder, and neurophysiological processing of threat cues in PTSD and their respective changes in the course of these two treatments (D-CPT and TAU).

**Discussion:**

The study will provide new insights in the understudied field of PTSD in adolescents and young adults. A newly developed intervention will be evaluated in this therapeutically underserved population. Results will provide data on treatment efficacy, direct and indirect treatment costs, as well as on associations of treatment outcome and PTSD intensity both to epigenetic profiles and to the neurobiological processing of threat cues. Besides, they will help to learn more about the psychopathology and possible new objective correlates of PTSD.

**Trial registration:**

Germanctr.de identifier: DRKS00004787.

## Background

Unfortunately, traumatic experiences in childhood and adolescence are common: a meta-analysis based on 65 international studies indicates that nearly 20% of women and 8% of men experienced sexual abuse prior to the age of 18 [1]. Regarding physical abuse in Western and European nations, numbers range from 3.6% to 16.3% [2-5]. These negative childhood experiences do not only have short-term consequences concerning the victims’ mental health – they are also related to a number of psychiatric disorders during the whole life span [6]. Consequently, people exposed to childhood sexual abuse (CSA) have a 2.4 heightened risk for the development of psychopathology compared to those without such experiences. For childhood physical abuse (CPA), this factor is around 1.5 [7]. In a meta-analysis, mortality and morbidity, drug and alcohol misuse, risky sexual behavior, obesity, and criminal behavior were found as consequences of childhood maltreatment [8]. According to Cutajar et al. [9], CSA increases the risk for several mental diseases like psychosis, affective, anxiety, substance abuse, and personality disorders. There is a particularly high probability for the development of post-traumatic stress disorders (PTSD) – exposure to CSA leads to an increased PTSD risk of 5.6 compared to non-CSA exposure. Accordingly, international studies show a high prevalence for PTSD after CSA, which ranges from 37% to 44% [10,11]. However, victims of CSA do not only suffer from PTSD; comorbidity secondary to PTSD often develops during adolescence and early adulthood, moderated by the patient’s efforts to fight painful trauma-related emotions, for instance by using harmful substances and by developing suicidal, self-injurious, or other severely dysfunctional behavior [12,13]. Early pregnancies and re-victimization occur at higher odds than in the general population [14,15].

Given these negative consequences, it is obvious that abuse-related PTSD should be treated at an early stage. For children, there already exist evaluated interventions: a meta-analysis of 39 studies analyzing treatment results for children and adolescents with psychiatric symptoms after CSA reported a general effect size of *g* = 0.77 for PTSD symptoms in the 5 studies with controlled designs and an untreated comparison control group. For the other studies, the authors report pre-post effect sizes of *g* = 1.13 for PTSD [16]. In contrast, few randomized controlled trials (RCTs) for PTSD therapy of adolescents were included in this meta-analysis – only two studies enrolling adolescents over 14 years of age used control conditions (waiting list/supportive treatment) and randomization [17,18]. However, as the mean age in both studies was around 11 years, the majority of participants were children. To our knowledge, there exist only five studies examining treatment effects on post-traumatic stress symptoms after CPA or CSA among adolescent patients exclusively [19-23]. Being the first of their kind, these studies are undoubtedly important. However, most of them have methodological deficits like caseness not defined by PTSD diagnoses or the use of insufficient diagnostic instruments. Only the study of Foa et al. [23] meets the standards for controlled studies, although it only focusses on girls. In summary, adolescents beyond the age of 14 are inadequately represented in PTSD research so far.

Thus, the major goal of the presented project herein is to provide information on treatment efficacy in this understudied group. A highly effective cognitive behavioral therapy manual for adults, Cognitive Processing Therapy (CPT [24]), was adapted for adolescent patients with CSA/CPA-related PTSD [25] – the Developmentally Adapted Cognitive Processing Therapy (D-CPT). Four major adjustments were integrated in the protocol. First of all, the treatment intensity was increased by administering the middle part of the protocol in high frequency (approximately 15 sessions during four weeks) to enhance the adolescents’ motivation; applying treatment in such intensity was reported to be superior to the usual scheme of one session per week [26]. Second, a commitment phase was included in the protocol in order to further build treatment motivation and to enhance therapeutic alliance as well as to establish the formal framework that is needed to conduct therapy. As survivors of childhood abuse often experience difficulties in emotion regulation, behavior and emotion management techniques, as used within Dialectical Behavior Therapy for PTSD (DBT-PTSD [27,28]), were also integrated in D-CPT. Finally, special consideration was given to developmental tasks affecting the patient’s entire life, such as career choice, vocational training, and romantic relationships. Adolescent patients are at high risk of school or secondary education drop out, of starting relationships with abusive partners, or of becoming re-victimized. Therefore, we decided to specifically address these issues at the end of treatment.

D-CPT has already been successfully piloted; nearly all of the 12 participating patients showed large reductions of post-traumatic stress symptoms and, moreover, comorbid symptoms improved significantly as well [25]. In October 2012, our research group started its work on the RCT and the associated studies. This article introduces its study protocol.

### The current trial

The overall aim of this RCT is to demonstrate the efficacy of a newly adapted psychotherapy intervention protocol in comparison to treatment as usual (TAU) in the understudied population of physically and sexually abused adolescents and young adults suffering from PTSD. Severity of PTSD symptoms before and after therapy serves as a primary outcome. Secondary goals are to evaluate changes in general psychopathology and comorbidity, such as depression, borderline personality features, and dissociation. Thirdly, the trial will allow for an estimation of the efficacy of TAU in Germany, on which currently no data is available.

Adjunct projects will provide new insights in questions beyond treatment efficacy; electroencephalographic (EEG) parameters are collected in an experiment which aims to find neuronal correlates of threat processing evoked by different categories of emotional words. Preliminary studies could show that anxiety disorders modify the way threatening information is processed [29]. By adapting these studies to the current project, multiple research questions may be answered. Namely, it will be possible to investigate differences in information processing between healthy subjects (control group), traumatized but healthy subjects (trauma control group), and traumatized subjects with PTSD (experimental group). In addition to this, the influence of D-CPT on information processing can be assessed on a psychophysiological level.

On the basis of questionnaires and videotaped sessions, potential predictors of treatment success are analyzed. As there is little research about handling PTSD in adolescents, also important variables influencing therapy outcome, such as treatment adherence, therapist competence, and working alliance, are not well studied [30]. Equally sparse is data about societal costs for the treatment of PTSD and/or mental comorbidities like depression or anxiety disorders (direct costs) as well as PTSD-related loss of productivity (indirect costs). No study has ever investigated the indirect costs resulting from PTSD in adolescents and, so far, no study has analyzed any cost data of PTSD or PTSD-treatment in Germany. Using different questionnaires, these issues are addressed in the D-CPT-project.

Concerning the genetic basis of PTSD and therapy outcome, there are only very few (though promising) clinical studies indicating epigenetic changes in PTSD in humans (for example [31]). In our study, the analysis of epigenetic profiles of PTSD patients by saliva samples during the course of therapy is realized via high-throughput epigenetic profiling.

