## Methods/design

### Trial design

D-CPT is an open, rater-blinded, multicenter, 2-arms RCT comparing D-CPT to TAU in Germany. There are five assessments: at baseline, within the treatment (approx. 8 weeks after beginning), directly after end of treatment (post-treatment) as well as 3 and 6 months after end of treatment (follow-up 1 and 2).

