### Participants

Adolescents and young adults aged 14 to 21 years may take part in the study. For inclusion, PTSD as a primary diagnosis after experiencing CSA and/or CPA beyond the age of three, according to the definition of the American Psychological Association [32], is required. To be diagnosed with PTSD, patients must meet 1 B-criterion, 2 C-criteria, and 2 D-criteria in the Clinician Administered PTSD Scale for Children and Adolescents (CAPS-CA [33]). A stable psychopharmacological medication is necessary at study entry, i.e., in the last 3 weeks there was either no or a constant psychopharmacological medication. Moreover, living in safe conditions, a sufficient knowledge of German language, as well as an informed consent from the parents/legal guardians (if under 18) and the participant is compulsory.

Exclusion criteria are:

• Acute suicidality within the last 6 months

• Life threatening self-harming behavior within the last 6 months

• Substance-related or organic mental disorder

• Pervasive developmental disorder

• Acute or lifetime diagnosis of a psychotic disorder according to the Diagnostic and Statistical Manual of Mental Disorders, Fourth Edition (DSM-IV-TR [34])

• Acute or lifetime diagnosis of a bipolar disorder according to DSM-IV-TR

• Current diagnosis of substance dependence according to DSM-IV-TR (abstinence <6 months)

• Mental retardation (IQ ≤75)

• Simultaneous psychological or psychiatric treatment

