### Planned interventions

Patients are enrolled either to TAU or D-CPT. Patients in TAU will be advised to look for treatment with other therapists in the respective areas. A detailed instruction to find a psychotherapist via internet will be given to the client by the coordinator of the respective study center. TAU patients will be monitored at the corresponding measurement points planned for D-CPT. After follow-up 1, patients can be enrolled into D-CPT if they wish to do so.

D-CPT is organized into four phases [25]. The treatment begins with a commitment phase comprising 5 sessions in 4 weeks. The aim of this phase is to build a therapeutic alliance and to increase and test the adolescents’ motivation for treatment. Safety plans are developed and anti-suicide contracts are signed. In phase 2, patients learn to tolerate and control intensive trauma-related emotions without acting in a dysfunctional way. For this reason, an emotion regulation training based on DBT-PTSD [27] is applied with 6 sessions in 4 weeks. Phase 3 comprises 15 sessions of CPT, according to Resick et al. [24], administered in high frequency (within 4 weeks); this is the central part of D-CPT. Dysfunctional beliefs related to the traumatic experiences are identified and modified by cognitive restructuring. In the last phase of treatment, developmental tasks specific to adolescence are introduced in 4 sessions during 4 weeks (one weekly session). The goal of this final therapy phase is to minimize the risk of future victimization and/or to prevent the choice of abusive partners. Moreover, the last treatment sessions focus on supporting the patient to complete education and to get an adequate vocational training. In sum, D-CPT comprises 30 sessions with 6 optional sessions for crisis intervention or communication with care givers or other institutions. Table 1 summarizes the treatment design and content. Adherence to D-CPT will be ensured by manualization, continuous local as well as central supervision, and ratings of therapeutic adherence and competence of random samples of videotaped sessions. Therapists are trained within one 4-day and one 2-day workshop. After attending the first workshop, every therapist treats at least one pilot case.

**Table 1 T1:** Overview of D-CPT

**Week**	**Sessions**	**Phase**	**Details**
1–4	5	Commitment	Therapy contract, emergency plan
			Lifeline
			Therapy goals

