## Discussion

Although the severe psychopathological consequences of sexual and/or physical abuse are known, only few studies report on the results of trauma focused psychotherapy for adolescents [19-23]. Consequently, chances were hitherto missed to administer effective treatments in early life to prevent the development of severe comorbidity or re-victimization. Reasons for the lack of studies are manifold, and might be due to difficulties in psychological assessments differing for adolescents and young adults, as well as to legal issues around different licensing procedures for therapists treating children and adolescents and those treating adult patients. Moreover, the lack of studies might be related to the characteristics of adolescents, whose motivational instability, rapid and intensive mood changes, and disentanglement from family structures have the potential to impede treatment participation and completion. The only published study on a similar methodological level needed 6 years of randomization to finally include 61 adolescent girls [23]. This highlights once more the specific problems in this age group. To bridge this knowledge gap by introducing a developmentally adapted CPT is the goal of the D-CPT network. The novelty of D-CPT is the adaption of the CPT procedure to the group of traumatized adolescents by increasing treatment intensity, integrating emotion-regulation-training, and finally by considering developmental tasks. The overall aim of the project is to evaluate this new therapy. Besides, the network aims to address several other heavily underexplored issues like variables influencing treatment outcome, epigenetics, health economics, and neurophysiological processing.

Taken together, the innovative character of our project is represented in i) a study sample of adolescents and young adults suffering from PTSD, ii) the developmentally adapted version of CPT (D-CPT) whose feasibility for youth within the German health system will be evaluated, and iii) measurement of the so far unknown effectiveness of TAU in Germany, which will be estimated.

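### The two-arm design cannot estimate the efficacy or effectiveness of TAU; it gives only an uncontrolled pre-post change in the TAU arm

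*Protocol article*

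**What the plan says.** The current trial names three goals. The third is: "Thirdly, the trial will allow for an estimation of the efficacy of TAU in Germany, on which currently no data is available". The Discussion lists among the project's innovative features the "measurement of the so far unknown effectiveness of TAU in Germany, which will be estimated".

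Trial design describes the study in these terms: "D-CPT is an open, rater-blinded, multicenter, 2-arms RCT comparing D-CPT to TAU in Germany". Statistical analysis sets one confirmatory test, a t-test of post-treatment CAPS-CA between those two arms, and makes everything else exploratory.

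Planned interventions defines the comparator: "Patients in TAU will be advised to look for treatment with other therapists in the respective areas". Help is limited to search instructions: "A detailed instruction to find a psychotherapist via internet will be given to the client by the coordinator of the respective study center". On timing: "TAU patients will be monitored at the corresponding measurement points planned for D-CPT". On later access: "After follow-up 1, patients can be enrolled into D-CPT if they wish to do so".

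Entry requires a current diagnosis (Participants): "To be diagnosed with PTSD, patients must meet 1 B-criterion, 2 C-criteria, and 2 D-criteria in the Clinician Administered PTSD Scale". Patients already in psychological or psychiatric care are excluded. Service use is recorded with a modified CSSRI before treatment, after treatment and at both follow-ups (Secondary outcome; Procedure).

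**The concern.** The efficacy of a treatment is its effect against what would have happened without it. Estimating that needs a comparator that does not receive the treatment. Here both randomised arms are active or self-sought care, and no group of PTSD patients is followed without either. The healthy and traumatised-but-healthy groups in The current trial belong to the EEG experiment and do not have PTSD, so they cannot fill that place.

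The plan would therefore attach the word efficacy, or effectiveness, to an uncontrolled change. The article says that no data exist on TAU in Germany, so whatever number the trial reports could be taken up as the reference value for usual care in this population. A plain pre-post change is likely to be misread in that role.

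**Working it through.** **1. The plan's own figure.** Inputs from Sample size calculation: alpha 0.05, power 0.8, d = 0.9 for D-CPT, d = 0.3 for TAU, 45 per arm. Sidedness is not stated; two-sided is assumed.

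- Difference = 0.9 − 0.3 = 0.6.
- Normal approximation: n = 2 × (1.96 + 0.84)² / 0.6² ≈ 43.6, so 44 per arm.
- Exact t-test: 44.6, so 45 per arm, with power 0.804 at 45.

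The stated 45 reproduces (one-sided gives 35 and does not). It rests wholly on the contrast between the arms, and nothing in it provides a contrast for TAU itself.

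**2. What the TAU arm's mean change contains.** Write natural course as N, regression to the mean as R, the share of patients who receive care as u, and the mean effect in those patients as E, all in SD units:

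observed change = N + R + u × E

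The trial observes the left side. N and R cannot be recovered without an untreated PTSD group. R is plausible because patients enter by meeting symptom thresholds on the CAPS-CA, the instrument that is also the outcome.

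**3. Size of the ambiguity from N + R.** Take the planning value 0.3 as the observed change. The documents give no untreated change, so the range is assumed.

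| N + R (assumed) | Part due to TAU |
|---|---|
| 0 | 0.3 |
| 0.1 | 0.2 |
| 0.2 | 0.1 |
| 0.3 | 0 |

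This is bias, so a larger sample would not reduce it.

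**4. Sampling error, which is a separate matter.** The half-width of a 95% interval for the mean change with n = 45 is 1.96 × √(2(1 − r)/45), where r is the pre-post correlation (assumed):

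- r = 0.3: 0.35 SD, interval −0.05 to 0.65
- r = 0.5: 0.29 SD, interval 0.01 to 0.59
- r = 0.7: 0.23 SD, interval 0.07 to 0.53

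At r = 0.5 and 0.7 the interval excludes zero. Even then it shows only that symptoms changed. It does not show that TAU changed them.

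**5. Unknown uptake (supporting point).** TAU patients start without ongoing care, must find a therapist, and are measured at the points planned for a 16-week course (Table 1). Set N + R = 0, so that E = 0.3 / u. With u assumed:

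- 100%: 0.3
- 75%: 0.4
- 50%: 0.6
- 25%: 1.2

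The same arm-level change fits very different effects of care actually received. The CSSRI can describe u afterwards, but it cannot supply N or R.

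**6. The primary comparison.** Randomisation gives both arms the same expected N and R, so these cancel in the D-CPT versus TAU difference. Optional entry into D-CPT comes after follow-up 1, later than the post-treatment endpoint.

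**The case against.** The strongest reply is that the article uses efficacy loosely. Sample size calculation gives each arm its own effect size and says that none exists for TAU in Germany, so the aim may mean only that arm-level change. The trial can indeed supply that number up to follow-up 1, and this part stands. It does not rescue the wording. The Background itself separates effects from controlled studies with an untreated comparison (g = 0.77) from pre-post effects in other studies (g = 1.13). The gap of 0.36 comes from different studies and does not measure natural change, but the article does treat the two kinds of figure as distinct.

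A second reply is that seeking a therapist in one's area is what usual care can look like, with incomplete uptake as part of it. That is fair. Self-sought care is a legitimate comparator, so the missing untreated group is the decisive reason and uptake only a supporting one.

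A reader might go further and infer that the TAU arm is mostly untreated, in effect a waiting list, and that the primary result is compromised. The documents do not support this. They give no uptake figure. Patients do receive search instructions. D-CPT is an option only after follow-up 1, and an influence on earlier care-seeking is conjecture. The hypothesis is stated as superiority to TAU, and the article says openly what TAU consists of.

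**Conclusion.** The aim is wrong as written in two places. The design supports a description of symptom course under TAU and an estimate of D-CPT relative to TAU. It does not support an estimate of the efficacy or effectiveness of TAU. The conclusion rests on the two-arm design and on selection for current PTSD, both stated in the article, and an analysis plan could not supply the missing comparator.

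Its size cannot be fixed from the documents. Under the assumed range of 0 to 0.3 SD for untreated change, anything from all to none of a 0.3 change could be due to TAU. The correlations and uptake shares used above are also assumptions.

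The consequence is confined to what may be concluded about TAU, a third-listed and non-confirmatory aim. The confirmatory test, its endpoint and the 45 per arm are untouched.

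**What to change.** In The current trial and in the Discussion, replace the aim with: *to describe the symptom course (uncontrolled pre-post change) up to follow-up 1 and the services used by patients assigned to TAU*. Make no efficacy or effectiveness claim for TAU. Report that change alongside the care actually received, as recorded by the CSSRI. The limit at follow-up 1 is needed because the TAU arm may contain D-CPT afterwards.

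An untreated arm is not needed. For scale, detecting d = 0.3 against one would take 2 × (1.96 + 0.84)² / 0.3² ≈ 174.4, so 175 per arm, and 45 per arm would have power of about 0.3.

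The cost is rewording in two places and a more modest tertiary aim. No new data, patients or assessments are required. With 31 of 90 participants recruited at the time of writing (Trial status), the change can be made before the results are known.
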